### Baseline characteristics of the participants

Sociodemographic Data: Name, gender, age, height, weight, education level, marital status, occupation, etc.

Disease-related Data: Tumor location, date of surgery, preoperative diagnosis, TNM staging, clinical stage, planned surgical method, whether preoperative neoadjuvant chemotherapy was performed, number of lymph nodes dissected, whether axillary radiotherapy is required during the intervention period, etc.

### Outcome measurement

#### Measurement timepoint

T0 (Baseline phase): Before treatment.T1-T4 (Inpatient treatment phase): From the preoperative day to postoperative day 3.T5-T12 (Outpatient treatment phase): From the 1st to the 8th scheduled visit.T13-T29 (Follow-up phase): From the 1st to the 17th follow-up.

### Primary outcome

The incidence and time of onset of lymphedema from the postoperative period until the end of follow-up.

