**Methods and analysis:**

A total of 72 breast cancer participants scheduled for axillary lymph node dissection will be recruited from Yunnan Provincial Hospital of Traditional Chinese Medicine and the First Affiliated Hospital of Kunming Medical University. They will randomly assigned in a 1:1 ratio to the TEAS group or the Sham TEAS group, with 36 cases in each group. Treatment will be administered once daily from the first day before surgery to the third day after surgery (paused on the surgery day), and subsequently twice a week for 4 consecutive weeks, totaling 12 intervention sessions. This will be followed by an 18-month follow-up period. The primary outcome measures are the incidence and time of onset of lymphedema within 18-month postoperatively. Secondary outcome measures include: VAS scores for perceived swelling and lymphedema-related symptoms evaluated at baseline (T0), from preoperative to postoperative day 3 (T1-T4), upon completion of twice-weekly post-discharge treatments (T5-T12), and during monthly follow-ups until 18 months postoperatively (T13-T29); changes in circumference, edema stage, and severity of the affected limb evaluated at T0, before and after treatments from preoperative to postoperative day 3 (T1a/b-T4a/b), before and after twice-weekly post-discharge treatments (T5a/b-T12a/b), and at T29; skin thickness ultrasound and lymphangiography of the affected limb performed at T0, T2, T12, and T29; and serum inflammatory factor levels measured at T0, T4, and T12. Adverse events occurring during the trial will be recorded.

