### Data analysis

Software and Data Handling: All statistical analyses will be performed by an independent statistician using SPSS 25.0 software (IBM, Armonk, NY). Missing data will be imputed using the Last Observation Carried Forward (LOCF) method.

Normality and Continuous Variables: Measurement data will be assessed for normality using the Shapiro-Wilk (S-K) test. Data conforming to a normal distribution will be expressed as mean ± standard deviation (SD). Intra-group comparisons (pre- and post-treatment) will be analyzed using the paired samples t-test, while inter-group comparisons will be performed using the independent samples t-test. Measurement data that does not follow a normal distribution will be analyzed using non-parametric rank-sum tests.

Categorical Variables and Significance: Enumeration data (categorical data) will be presented as percentages or constituent ratios, and differences between groups will be analyzed using the Chi-square (χ²) test. All statistical tests will be two-sided, with the significance level set at αt 0.05. A P-value < 0.05 will be considered statistically significant.

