The primary objective of this study is to determine the efficacy of TEAS for BCRL. In addition to recording subjective indices (e.g., VAS scores for perceived swelling and lymphedema-related symptoms) and objective clinical parameters (e.g., limb circumference changes and edema staging), this study highlights the crucial role of lymphatic system visualization and morphological monitoring in early diagnosis and assessment. Given that the initial pathological changes in lymphedema often manifest as slight thickening of the skin rather than an increase in subcutaneous tissue volume, this study incorporates ultrasound monitoring of skin thickness to provide early morphological evidence that is more sensitive than circumference measurements (23). Furthermore, to objectively assess the immediate impact of surgery on the lymphatic system, this study emphasizes the importance of preoperative baseline (T0) assessment. Serial near-infrared (NIR) fluorescence imaging, performed pre- and post-operatively (24), enables the dynamic observation of functional lymphatic vessel damage and the subsequent formation of collateral circulation. NIR possesses excellent tissue penetration, sensitivity, and high resolution, enabling non-invasive real-time tissue imaging. Indocyanine green (ICG) is a common NIR fluorescent dye used in BCRL assessment. Upon subcutaneous injection, ICG binds to plasma proteins in lymph, emitting detectable fluorescent signals that are transduced into lymphatic system images (25). The advantages of fluorescence imaging include the absence of ionizing radiation, minimal trauma, repeatability, real-time imaging, and ease of operation, making it suitable for preoperative assessment, intraoperative tracing, and postoperative follow-up. Furthermore, to comprehensively evaluate the intervention, this study will investigate the impact of TEAS on serum inflammatory factor levels. Finally, we will evaluate the statistical differences between TEAS and sham TEAS regarding BCRL incidence and quality of life.

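### Two primary outcomes share an unadjusted two-sided 0.05 with no rule for which decides the trial; if either suffices, the false-claim risk is above 5% and at most about 10%

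*Protocol article*

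**What the plan says.** The Primary outcome section gives "The incidence and time of onset of lymphedema from the postoperative period until the end of follow-up". The Methods and analysis part of the abstract puts it in the plural: "The primary outcome measures are the incidence and time of onset of lymphedema within 18-month postoperatively". Neither place says which of the two decides the trial.

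The Data analysis section sets the significance rule for every test: "All statistical tests will be two-sided, with the significance level set at" 0.05, followed by "A P-value < 0.05 will be considered statistically significant".

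The same section assigns tests by type of data, not by outcome. For categorical data, "differences between groups will be analyzed using the Chi-square (χ²) test". For normally distributed measurements, "inter-group comparisons will be performed using the independent samples t-test". Otherwise, "Measurement data that does not follow a normal distribution will be analyzed using non-parametric rank-sum tests". No survival method is listed. The article does not say which test applies to time of onset, or how women who never develop lymphedema enter that comparison.

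**The concern.** With two primary outcomes, one uncorrected threshold and no success rule, the trial has two chances to report a positive primary result. The text lets the authors claim prevention on whichever outcome reaches P<0.05.

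The two results can also disagree. Incidence might be equal in both arms while onset is later among TEAS cases, or incidence might fall while onset among the remaining cases is earlier. The plan does not say whether either pattern counts as prevention.

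The first pattern is the more troubling. A comparison of onset restricted to women who developed lymphedema conditions on something that happens after randomisation. The groups compared are no longer the randomised groups, so the result should not carry an efficacy claim by itself.

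**Working it through.** **Inputs from the article.** Two primary outcomes (Primary outcome section; abstract). Two-sided 0.05 for each test (Data analysis). 30 per group before dropout, 36 enrolled (Sample size calculation). Follow-up of 18 months (Follow-up). Incidence of about one quarter (Discussion) and 58.3% after axillary dissection (Introduction).

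**Assumptions.** A middle incidence of 40%, and the distribution of onset times.

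**The plan's own figure.** 30 × 2 × 1.20 = 72. This reproduces, and it uses neither alpha nor power. The article states no family-wise error rate to reproduce.

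**Bounds, if either result suffices.**
- Upper bound for any dependence: 0.05 + 0.05 = 0.10.
- Independent tests: 1 − 0.95² = 0.0975.
- Identical tests: 0.05.
- If both results were required, the error could not exceed 0.05.

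**Effect of correlation between the two test statistics (bivariate normal).**

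| Correlation | Chance that at least one is significant |
|---|---|
| 0 | 9.75% |
| 0.5 | 9.1% |
| 0.7 | 8.4% |
| 0.8 | 7.8% |
| 0.9 | 7.0% |
| 0.95 | 6.5% |

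**Simulation with no treatment effect.** 30 or 36 per arm; incidence 25%, 40% or 58.3% in both arms; exponential onset; 4,000 trials per setting; simulation standard error about 0.35 to 0.5 percentage points. Incidence is tested by chi-square without continuity correction.

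| How onset is analysed | Incidence or onset significant |
|---|---|
| t-test, cases only | 9.25% to 10.55% |
| rank-sum, cases only | 8.70% to 10.03% |
| log-rank, all participants | 4.95% to 7.15% |
| rank-sum, all participants, non-cases set to 18 months | 5.20% to 7.88% |

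Values just above 10% or below 5% are within simulation error of those limits. A second simulation, with onset uniform over months 1 to 18, gave 9.1% to 9.9% for the t-test among cases and 5.1% to 6.2% with log-rank. The shape of the onset distribution therefore matters little. What matters is who enters the onset comparison.

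**Effect of how onset is dated.** Limb circumference, stage and severity are recorded up to the last treatment visit, at about one month, and then only at 18 months. The monthly contacts between collect swelling and symptom scores. If onset is dated from the limb assessment, every later case is dated month 18, and a cases-only rank-sum test has little to compare. The same arm sizes and incidences, with an assumed share of cases dated in the first month, give:

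| Share dated in month 1 | Incidence or onset significant |
|---|---|
| 0% | about 5% |
| 5% | about 5% to 6% |
| 10% | about 5.5% to 8% |
| 20% | about 7% to 9.5% |

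The Follow-up section puts typical onset at 3 months or later, so low early shares are plausible. If onset is dated from the monthly symptom scores instead, this reduction does not apply.

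**After the fix.** At 0.025 each: 1 − 0.975² = 4.94% if independent, and at most 0.025 + 0.025 = 5% in any case. One named primary, or a fixed order: 5%.

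**The case against.** The strongest reply is that the article fixes no error rate for the pair. It never assigns a test to time of onset and never says that women without lymphedema are left out. Whether and when lymphedema occurs are two views of one event, so an analysis of everyone would be strongly correlated with incidence and the inflation modest. This stands, and it is why the size must be given as a range.

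A second reply is that 0.05 is a per-test level and that no sentence says one positive result is enough. This also stands: the plan does not break a family-wise promise, because it makes none. But it does not require both results either, and its only rule calls each one significant by itself.

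A third reply is that multiplicity rules often sit in the statistical analysis plan, which is not shown, and that the sample size section calls the work exploratory. This carries less weight. The choice of the deciding primary outcome belongs in the protocol, and this one has already published both the pair and the threshold. The exploratory label justifies the sample size, while the abstract and Discussion set out to determine efficacy.

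A reader might also take the closing statement of aims in the Discussion, "Finally, we will evaluate the statistical differences between TEAS and sham TEAS regarding BCRL incidence and quality of life", as evidence that two primaries will be tested. It is not. It names incidence but not onset and, if anything, leans towards incidence as the deciding result.

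**Conclusion.** The point holds in a limited form. Two primary outcomes are named, each is declared significant at two-sided 0.05, and no order, split or both-must-succeed rule is given. If either can support the efficacy claim, the chance of a false claim is above 5% and at most about 10%:

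- about 9-10% if onset is compared among cases only and onset times are well spread;
- about 5-8% if all participants enter the onset analysis, or if no more than roughly a tenth of cases can be dated before month 18.

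These figures assume no treatment effect, incidence between 25% and 58.3%, and 30 to 36 women per arm.

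A reader might infer that the trial's error rate simply is 9-10%, nearly double what it states. The documents do not support that. The figure depends on a cases-only comparison, which is the natural reading of the listed tests but is not written down, and on a way of dating onset that is not specified. What is certain is that the deciding result is not identified and that the published rule permits a claim on either one.

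**What to change.** In the abstract and the Primary outcome section, choose one of two routes:

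1. Name one deciding primary, for example incidence of lymphedema by 18 months, TEAS versus sham, at two-sided 0.05. Make time of onset a key secondary outcome, tested for significance only if the primary is significant.
2. Keep both as primary, using Holm or 0.025 each.

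Amend the P<0.05 sentence in Data analysis so that it follows the chosen route and does not apply separately to each primary.

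On either route, analyse onset in all randomised participants as time to event, with women free of lymphedema censored, and not among cases only. Splitting the alpha alone would leave a comparison conditioned on a post-randomisation event as a primary result. State also which assessment dates the onset.

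The cost is protocol and analysis-plan wording, with no extra patients. The total of 72 does not depend on alpha and is unchanged. The downside is that on the first route a significant onset result alone can no longer support an efficacy claim, and on the second the primaries face a stricter threshold. Recruitment is under way (10 enrolled by July 2025), so the choice should be recorded before any unblinded result is seen.

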### Secondary outcomes

Visual Analogue Scale (VAS) for Perceived Swelling: Changes in the VAS score for perceived swelling will be observed at the following time points: before treatment (T0), from preoperative to postoperative day 3 (T1-T4), upon completion of twice-weekly post-discharge treatments (T5-T12), and during monthly follow-ups until 18 months postoperatively (T13-T29). Data will be recorded in the VAS data collection form (see **Figure 3** and **Table 2**).

**Figure 3 f3:**
[figure not shown]
Visual simulation score.

**Table 2 T2:** Data collection form for visual analogue scale (VAS) of perceived swelling.

Name: Age: Operated limb: Date of surgery:					
Assessment timepoint	0 Points No swelling	1-3 Points mild swelling, tolerable	4-6 Points intermittent swelling, does not affect rest	7-9 Points marked swelling, affects rest, difficult to tolerate	10 Points severe swelling, unbearable, affects daily life (sleep, activity, diet, etc.)
Preoperative (T1)					
Postoperative Day 1 (T2)					
Postoperative Day 2 (T3)					
Postoperative Day 3 (T4)					
Scheduled Treatment 1 (T5)					
Scheduled Treatment 2 (T6)					
Scheduled Treatment 3 (T7)					
Scheduled Treatment 4 (T8)					
Scheduled Treatment 5 (T9)					
Scheduled Treatment 6 (T10)					
Scheduled Treatment 7 (T11)					
Scheduled Treatment 8 (T12)					
Follow-up 1 (T13)					
Follow-up 2 (T14)					
Follow-up 3 (T15)					
Follow-up 4 (T16)					
Follow-up 5 (T17)					
Follow-up 6 (T18)					
Follow-up 7 (T19)					
Follow-up 8 (T20)					
Follow-up 9 (T21)					
Follow-up 10 (T22)					
Follow-up 11 (T23)					
Follow-up 12 (T24)					
Follow-up 13 (T25)					
Follow-up 14 (T26)					
Follow-up 15 (T27)					
Follow-up 16 (T28)					
Follow-up 17 (T29)					

Lymphedema-related Symptoms: Lymphedema-related symptoms will be observed at baseline (T0), from preoperative to postoperative day 3 (T1-T4), upon completion of twice-weekly post-discharge treatments (T5-T12), and during monthly follow-ups until 18 months postoperatively (T13-T29). The symptom scale includes items such as swelling, tightness, heat, firmness, numbness, heaviness, tingling, pain, general discomfort, distress, and weakness. Each item is scored on a scale of 0 to 10, where 0 indicates “no sensation” and 10 indicates “intense sensation” (see **Table 3**).

**Table 3 T3:** Data collection form for lymphedema-related symptom scores.

Name: Age: Operated limb: Date of surgery:											
Items	No sensation 								Intense sensation		
	0	1	2	3	4	5	6	7	8	9	10
Swelling											
Tightness											
Heat											
Firmness											
Numbness											
Heaviness											
Tingling											
Pain											
General discomfort											
Distress											
Weakness											
Total score											
Assessment timepoint	Swelling	Tightness	Heat	Firmness	Numbness	Heaviness	Tingling	Pain	General discomfort	Distress	Weakness
Preoperative (T1)											
Postoperative Day 1 (T2)											
Postoperative Day 2 (T3)											
Postoperative Day 3 (T4)											
Scheduled Treatment 1 (T5)											
Scheduled Treatment 2 (T6)											
Scheduled Treatment 3 (T7)											
Scheduled Treatment 4 (T8)											
Scheduled Treatment 5 (T9)											
Scheduled Treatment 6 (T10)											
Scheduled Treatment 7 (T11)											
Scheduled Treatment 8 (T12)											
Follow-up 1 (T13)											
Follow-up 2 (T14)											
Follow-up 3 (T15)											
Follow-up 4 (T16)											
Follow-up 5 (T17)											
Follow-up 6 (T18)											
Follow-up 7 (T19)											
Follow-up 8 (T20)											
Follow-up 9 (T21)											
Follow-up 10 (T22)											
Follow-up 11 (T23)											
Follow-up 12 (T24)											
Follow-up 13 (T25)											
Follow-up 14 (T26)											
Follow-up 15 (T27)											
Follow-up 16 (T28)											
Follow-up 17 (T29)											

Comparison of Limb Circumference Changes, Edema Staging, and Severity: Changes in the circumference, edema stage, and severity of the affected limb will be observed at baseline (T0), before and after treatments from preoperative to postoperative day 3 (T1a/b-T4a/b), before and after twice-weekly post-discharge treatments (T5a/b-T12a/b), and at 18 months postoperatively (T29). The mean values and differences in circumference before and after treatment will be compared between the two groups to evaluate the effect of treatment on limb edema. Staging and measurement standards are detailed in **Table 4**.

**Table 4 T4:** Data collection form for upper limb circumference, edema staging, and severity.

Name: Age: Operated limb: Date of surgery:													
Upper limb circumference measurement							Edema stage				Edema severity		
Measurement timepoint	Measured limb	Palmar crease	Wrist crease	10 cm above wrist crease	Elbow crease	5 cm above elbow crease	Stage 0	Stage I	Stage II	Stage III	Mild	Moderate	Severe
Preoperative (T1)	L												
	R												
Postoperative Day 1 Pre-treatment T2a	L												
	R												
Postoperative Day 1 Post-treatment T2b	L												
	R												
Postoperative Day 2 Pre-treatment T3a	L												
	R												
Postoperative Day 2 Post-treatment T3b	L												
	R												
Postoperative Day 3 Pre-treatment T4a	L												
	R												
Postoperative Day 3 Post-treatment T4b	L												
	R												
Scheduled Treatment 1 Pre-treatment T5a	L												
	R												
Scheduled Treatment 1 Post-treatment T5b	L												
	R												
Scheduled Treatment 2 Pre-treatment T6a	L												
	R												
Scheduled Treatment 2 Post-treatment T6b	L												
	R												
Scheduled Treatment 3 Pre-treatment T7a	L												
	R												
Scheduled Treatment 3 Post-treatment T7b	L												
	R												
Scheduled Treatment 4 Pre-treatment T8a	L												
	R												
Scheduled Treatment 4 Post-treatment T8b	L												
	R												
Scheduled Treatment 5 Pre-treatment T9a	L												
	R												
Scheduled Treatment 5 Post-treatment T9b	L												
	R												
Scheduled Treatment 6 Pre-treatment T10a	L												
	R												
Scheduled Treatment 6 Post-treatment T10b	L												
	R												
Scheduled Treatment 7 Pre-treatment T11a	L												
	R												
Scheduled Treatment 7 Post-treatment T11b	L												
	R												
Scheduled Treatment 8 Pre-treatment T12a	L												
	R												
Scheduled Treatment 8 Post-treatment T12b	L												
	R												
18 Months Postoperative (T29)	L												
	R												

Edema Staging:.

ISL Staging classifies lymphedema into 4 stages based on severity:

Stage 0: Latent or subclinical stage; no obvious limb swelling, no visible clinical symptoms.

Stage I: Obvious swelling with pitting edema; swelling subsides upon limb elevation.

Stage II: Swelling does not subside with elevation; early stage presents as pitting edema, while late stage becomes non-pitting due to subcutaneous fat deposition and fibrosis.

Stage III: Non-pitting edema with elephantiasis; skin thickening, roughness, folds, hyperpigmentation, loss of elasticity, and severe fibrosis.

Edema Severity:

Generally determined by comparing the circumference of the affected limb to the healthy limb at the same measurement point:

Mild edema: Circumference difference < 3 cm

Moderate edema: Circumference difference 3–5 cm

Severe edema: Circumference difference > 5 cm

Side of Affected Limb:

L, Left

R, Right

Measurement Instructions:

The patient should be in a sitting or standing position with arms hanging naturally. Use a soft, non-elastic tape measure to encircle and measure the fixed points on both upper limbs. Measurement Points: Palmar crease, Wrist crease, 10 cm above wrist crease, Elbow crease, and 5 cm above elbow crease. Note: To avoid error, measure each point 3 times and calculate the average. Ensure measurements are taken at a fixed time, using the same tape measure, in the same position, and preferably by the same person to guarantee data accuracy and consistency.

Skin Thickness Ultrasound Examination: Changes in the skin thickness of the affected limb will be measured using ultra-high-frequency ultrasound. The specific measurement locations are detailed in **Table 5**. These assessments will be performed at baseline (T0), on postoperative day 1 (T2), after the 12th treatment (T12), and at 18 months postoperatively (T29).

**Table 5 T5:** Patient upper limb skin thickness record form.

Name: Age: Operated limb: Date of surgery:						
Measurement of skin thickness in the patient’s upper limbs						
Assessment timepoint	Measured limb	Measurement point 1	Measurement point 2	Measurement point 3	Measurement point 4	Measurement point 5
Baseline (T0)	L					
	R					
Postoperative Day 1 (T2)	L					
	R					
Scheduled Treatment 8 (T12)	L					
	R					
18 Months Postoperative (T29)	L					
	R					

Side of Affected Limb:.

L, Left

R, Right

Measurement points:

(a) Arm positioned in supinated position: 1. Medial upper arm. 2. Lateral upper arm measuring points are placed 7 cm above the cubital crease. 3. Medial forearm. 4. Lateral forearm measuring points are placed 7 cm below the cubital crease. (b) Arm in pronated position: 5. Mid-point dorsal hand surface measuring point is placed between the wrist and the first metacarpophalangeal joint.

Measurement Instructions:

In the initial measurement position, participants were seated with their upper arm slightly abducted, elbow fully extended, and hand in supination. For the fifth measurement, participants placed their hands in a pronated position on the dorsal side of the hand.

Lymphangiography of the Affected Limb: Lymphatic system imaging will be performed at baseline (T0), on postoperative day 1 (T2), after the 12th treatment (T12), and at 18 months postoperatively (T29).

Serum Inflammatory Factor Levels: Peripheral venous blood samples will be collected at baseline (T0), on postoperative day 3 (T4), and at the end of treatment (T12). Serum levels of inflammatory factors, including Tumor Necrosis Factor-alpha (TNF-r-a high-sensitivity C-reactive protein (hs-CRP), and Procalcitonin (PCT), will be measured using ELISA. All blood samples will be sent to the laboratory for analysis and subsequently disposed of in accordance with relevant regulations.

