### Follow-up

Since the onset of lymphedema typically occurs between 3 months and 3 years postoperatively, peaking at 18 months (5), the follow-up period is established as 1.5 years postoperatively. From the completion of the intervention until 1.5 years postoperatively, follow-up will be conducted once a month via telephone or WeChat. The content of these follow-ups includes the visual analogue scale (VAS) for perceived swelling and lymphedema-related symptoms. Additionally, an in-person appointment will be scheduled at 1.5 years postoperatively to collect data on upper limb circumference, edema stage, and severity.

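### The stated circumference difference closes about one month after surgery and uses the affected arm only, so it measures a short-term effect; late swelling at 18 months (T29) has no stated contrast with baseline

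*Protocol article*

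**What the plan says.** All references are to the protocol article.

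- **Schedule and limb** (Secondary outcomes, circumference item). The outcome is worded for one arm: "Changes in the circumference, edema stage, and severity of the affected limb will be observed at baseline (T0"), then before and after each inpatient treatment, then "before and after twice-weekly post-discharge treatments (T5a/b-T12a/b), and at 18 months postoperatively (T29").
- **Comparison** (same item). "The mean values and differences in circumference before and after treatment will be compared between the two groups to evaluate the effect of treatment". No other circumference difference is stated.
- **Recording form** (Table 4). Rows for left and right arms at every occasion. T2 to T12 have separate pre- and post-treatment rows. T1 has a single row, T0 has none, and the last row is the unpaired "18 Months Postoperative (T29").
- **Measurement instructions** (Table 4). Staff are to "encircle and measure the fixed points on both upper limbs".
- **Severity grade** (notes to Table 4). "Generally determined by comparing the circumference of the affected limb to the healthy limb at the same measurement point", in three bands: under 3 cm, 3 to 5 cm and over 5 cm.
- **Skin thickness.** "Changes in the skin thickness of the affected limb will be measured using ultra-high-frequency ultrasound", at T0, T2, T12 and T29. Table 5 has left and right rows at each.
- **Timing** (Follow-up). "the onset of lymphedema typically occurs between 3 months and 3 years postoperatively", with a peak at 18 months. The only in-person follow-up after the treatment course is at 1.5 years. Under Treatment Course, the sessions end one month after the operation.

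**The concern.** In a prevention trial, an objective limb measure is useful mainly if it is contrasted at a time when the condition is expected to have appeared. The difference stated here is formed from readings taken while sessions are still being given. If treatment means a session, it captures what happens to the arm over a 30-minute procedure. If it means the course, it captures early postoperative change.

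The late reading is collected, but the text does not say what it is to be compared with. Without a reference to the person's own preoperative value or to the other arm, a comparison of T29 means carries all the ordinary variation in arm size between women. With 30 to 36 per group, that is a substantial loss of precision.

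What is at stake is interpretation. The Discussion lists limb circumference change among the objective parameters bearing on efficacy. A group difference in early or within-session change could be offered as support for prevention although it says nothing about swelling at 18 months.

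**Working it through.** **1. The plan's own figures.** Sessions: 1 preoperative + 3 postoperative + 8 scheduled = 12, as stated. Sample size: 30 × 2 × 1.20 = 72, as stated; it is used below only for group size.

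**2. When the before/after differences end.** The last session falls at about postoperative day 3 + 28 = day 31, or 31/30.4 ≈ 1.0 month. The onset window opens at 3 months, about day 91.

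- Session reading: every pair (a and b on the same day) lies at or before about day 31.
- Course reading: the difference runs from before the first session to T12, again about day 31.

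Both close about 60 days before the window opens.

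**3. Count of circumference readings.**

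| Source | Before/after pairs | Total occasions | Distribution |
|---|---|---|---|
| Text | 12 (T1 to T12) | 1 (T0) + 24 + 1 (T29) = 26 | 24 of 26 are session pairs |
| Table 4 | 11 (T2 to T12) | 1 (T1) + 22 + 1 (T29) = 24 | 23 of 24 within about one month of surgery |

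Both sources give no pair at T29. They disagree on T0 and on T1a/b. Because T1 is also a treatment day, Table 4's single T1 row does not show whether it precedes the first session.

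**4. What an unadjusted comparison of affected-arm means at T29 could detect.** Two-sided 0.05, 80% power, 30 per group: (1.960 + 0.842) × √(2/30) = 0.72 SD (0.66 SD with 36). The protocol gives no SD, so these inputs are assumptions: between-person SD s of 2.5 to 3.5 cm, correlation r between arms of 0.90 to 0.98.

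- Raw affected-arm mean: 0.723 × 2.5 = 1.8 cm to 0.723 × 3.5 = 2.5 cm.
- Affected minus healthy, SD = s√(2(1 − r)): from 2.5 × √0.04 = 0.50 cm to 3.5 × √0.20 = 1.57 cm, so 0.4 to 1.1 cm detectable.

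**5. What subtracting the healthy arm adds once change from baseline is used.** Assumed: lymphedema-related SD L = 1.0 cm, error SD e = 0.3 cm per reading, general arm-size change SD W. A raw change has two readings; an inter-arm change has four.

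- Raw change: L² + W² + 2e² = 1.18 + W²
- Inter-arm change: L² + 4e² = 1.36

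| W (cm) | Raw | Inter-arm | Effect of subtracting |
|---|---|---|---|
| 0.25 | 1.24 | 1.36 | about 9% worse |
| 0.50 | 1.43 | 1.36 | 5% better |
| 1.00 | 2.18 | 1.36 | 38% better |

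Break-even is at W² = 2e² = 0.18, that is W ≈ 0.42 cm.

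**The case against.** The best defence has five parts.

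- **T29 is not left out.** The text says circumference change is observed from T0 to T29 and that mean values are compared as well as differences. A group comparison at 18 months is therefore possible. This stands, but the comparison is not named, and as worded it has no reference to baseline or to the other arm.
- **The healthy arm is used.** A reader might infer that the plan ignores it. That is not so: the severity grade in the same outcome block compares the arms and is collected at T29. The grade is coarse, however. Its lowest band has no lower limit, and it does not subtract a difference between arms that was present before surgery.
- **Prevention is tested elsewhere.** A reader might infer that the trial cannot show prevention. The documents do not support that: incidence and time of onset are the primary outcome, and circumference is secondary.
- **Weight change does not create cases.** A reader might infer that a participant who gains weight would be counted as having lymphedema. Nothing in the protocol defines a case by raw affected-arm circumference, and randomization balances weight change on average. In a group comparison it adds noise, not bias.
- **An analysis plan may settle the contrast.** It may. But the protocol does more than leave the contrast open. It states one, and that one ends before the onset window on either reading.

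The measurement instructions (fixed posture, three readings averaged, same tape) also limit tape and posture error.

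**Conclusion.** The point holds in a limited form. The only circumference difference that the protocol states is an affected-limb difference before and after treatment, which ends at about day 31. It therefore reflects a short-term effect and does not test late swelling. The finding on timing rests on the protocol's own dates and needs no assumption.

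For skin thickness only the inter-arm part applies, because its schedule has no session pairs and already includes T0 and T29.

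The size of the precision gain is illustrative, since every SD and correlation is assumed. Most of the gap between 1.8–2.5 cm and 0.4–1.1 cm comes from removing between-person arm size, which a preoperative reference would also largely do. The further benefit of the healthy arm depends on how much general arm size changes over 18 months, and it is slightly negative if that change is small. The weakness concerns one secondary outcome and how its result may be read; it does not undermine the primary outcome. It is still worth correcting, because the better definition uses data already being collected.

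**What to change.** 1. **Circumference.** Define the outcome as the change from the preoperative reading in the affected-minus-healthy difference at the named measurement points. Compare groups at T29 (key) and at T12a (early, before the session), adjusting for the preoperative difference.
2. **Skin thickness.** Define it in the same way from the left and right rows of Table 5.
3. **Within-session a/b differences.** Keep them, labelled as an exploratory measure of acute effect that does not support a preventive claim.
4. **Text and Table 4.** Reconcile T0 and T1a/b, and state which reading, taken before the first session, is the preoperative reference.

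Cost: wording of the outcome and its analysis only, since both arms are already scheduled at these visits. Trial status reports 10 participants enrolled as of July 2025, so the change can be made early. The statistical price is the small added measurement noise shown above (about 9% more variance in the least favourable scenario) if general arm-size change turns out to be small.
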